### Participants

We will recruit two participant groups of equal size with differing diagnostic status: one group of individuals with clinically relevant depressive symptomatology and a control group of individuals without depression. The diagnostic groups will be matched according to gender and age. For the depression group, the main inclusion criterion is the presence of a diagnosis from the depressive spectrum according to ICD-10 criteria (F32 ‘depressive episode’, F33 ‘recurrent depressive disorder’, F34.1 ‘dysthymia’, and F43.20 & F43.21 ‘adjustment disorder with depressive symptoms’ [38]) according to the Structured Clinical Interview for DSM-5 Disorders - Clinician version (SCID-5-CV; German Version: [39]). The main inclusion criterion for the group without depression is a score < 10 on the Patient Health Questionnaire (PHQ)-8 [40]. Additional inclusion criteria for both groups include being ≥ 18 years, being able and willing to provide informed consent regarding study participation, and having sufficient German language skills (at least level B2 according to the Common European Framework of Reference for Languages). Exclusion criteria included the presence of any psychotic disorder (ICD-10 F2x), any substance dependence disorder other than nicotine (ICD-10 F1x.2), acute suicidality, any impairment of facial expression (e.g., due to facial paralysis or recent Botox treatment or autism spectrum disorder), and any type of dyschromatopsia. To ensure maximum external validity, we refrain from applying further potential exclusion criteria such as other clinical comorbidities, or concurrent pharmaco- or psychotherapy, but will record this information.

A power analysis was conducted with G*Power [41] to determine the necessary sample size for a 2-group-comparison of each of the intervention conditions (CR, CR + AFE, AFE) with the sham control condition. In absence of similar studies serving as reference for the determination of a critical effect, a team of three clinical experts agreed that an effect size of *d* = 0.5 would be therapeutically relevant. The power analysis yielded a necessary sample size of *n* = 32 for each of the four intervention conditions and two diagnostic groups based on a 2-sided analysis, a critical alpha-level of α = 0.05, and a power of β = 0.80. Hence, we will include *N* = 256 participants in total, composed in equal parts of participants with depression (*n* = 128) and without depression (*n* = 128).

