### Measures

#### Demographic and health-related information, screening, and diagnostics

Demographic and health-related variables assessed include age, date of birth, German language skills, nationality, gender, height, weight, academic degree, professional occupation, current academic field, relationship status, lifetime diagnosis of a psychiatric disorder, as well as history of and current psychotherapy and medication treatment.

The PHQ-8 will be used to screen for current depressive symptomatology during online screening (T0). The 8-item self-report measure assesses the frequency of eight of the nine criteria for depression according to the DSM-5 [1] during the previous two weeks on a four-point Likert-scale (0 = *not at all* to 3 = *nearly every day*). In contrast to the PHQ-9 [49], the PHQ-8 does not assess suicidality or self-injury. To ensure provision of adequate psychological support when necessary, we exclusively assessed suicidality/self-injury while face-to-face with participants. Previous studies showed comparable validity of the PHQ-8 and PHQ-9 in assessing depression [40, 50]. The items of the PHQ-8 can be summed up to a total score with a maximum of 24. A score ≥ 10 indicates clinically relevant depression [40].

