#### Automated detection of depression

Machine learning methods will be implemented to examine the automated discrimination between individuals with and without depression based on kinesthesia and other psychophysiological data (i.e., facial expression and body posture from video data, facial muscle activity from EMG, respiration, heart rate (variability), and verbal acoustics from audio recordings). Initially, only video data (facial expression/body posture) will be used. Subsequently, psychophysiological data and verbal acoustics data will supplement the video dataset, providing additional modalities for analysis. Ultimately, our long-term goal is to adopt a multi-modal machine learning approach to leverage all data modalities available to enhance the accuracy and robustness of depression identification.

For the classification task (i.e., discrimination between individuals with and without depression), different machine learning pipelines will be trained. This will consist of different steps, from pre-processing and normalization to feature selection and actual classification. After the machine learning process, we will use explainable artificial intelligence techniques to identify discriminative features and to interpret the output of the machine learning models. To split the data into training and test sets, we will employ a standard train-test split using the scikit-lear library train_test_split function with a fixed random seed and allocating 80% of the dataset for model training and reserving 20% for evaluation. This approach ensures reliable performance estimation while guarding against overfitting. The performance of the classification models will be evaluated using established metrics such as sensitivity (i.e., $$\:\frac{number\:of\:true\:positives}{number\:of\:true\:positives+number\:of\:false\:negatives})$$ and specificity (i.e., $$\:\frac{number\:of\:true\:negatives}{number\:of\:true\:negatives+number\:of\:false\:positives}$$), which are indicative of the classification task’s performance with a benchmark of 80%. Furthermore, we will test whether the balanced accuracy (i.e., $$\:\frac{sensitivity\:+\:specificity}{2}$$) will exceed the null distribution.

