Additionally, we will predict depressive symptom severity using machine learning-based regression models. The training of the models for the regression task will follow the same steps as for the classification task. As error metrics for the correspondence between clinical and machine-learning data, we will use Mean Absolute Error (MAE) and Root Mean Squared Error (RMSE). We will evaluate different machine learning models for both classification and regression tasks, such as k-Nearest Neighbour, Support Vector Machines, Decision Trees, Random Forests, and Artificial Neural Networks, to select the best-performing model based on predefined error metrics.

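### Pooled MAE and RMSE with no comparator cannot show whether the severity regression measures severity or only recognises the diagnostic group

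*Protocol article*

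**What the plan says.** All references are to the protocol article.

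- **Participants.** The sample of 256 is "composed in equal parts of participants with depression" (128) and without (128). For the depression group "the main inclusion criterion is the presence of a diagnosis from the depressive spectrum according to ICD-10 criteria". For the other group: "The main inclusion criterion for the group without depression is a score < 10 on the Patient Health Questionnaire (PHQ)-8". Under Measures, a PHQ-8 score of 10 or more "indicates clinically relevant depression", so controls are selected on a severity score.
- **Automated detection of depression, target.** Beyond classification, "we will predict depressive symptom severity using machine learning-based regression models". The sentence does not name the severity instrument.
- **Same section, training.** "The training of the models for the regression task will follow the same steps as for the classification task". Those steps include a split "allocating 80% of the dataset for model training and reserving 20% for evaluation". No restriction to one diagnostic group is stated.
- **Same section, scoring.** For agreement between clinical and model-derived values, "we will use Mean Absolute Error (MAE) and Root Mean Squared Error (RMSE"). The best model is chosen on predefined error metrics.

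For classification the section sets 80% as the benchmark for sensitivity and specificity and tests balanced accuracy against a null distribution. It states no counterpart for the regression.

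**The concern.** The sample is built from two groups that should differ in mean severity. Part of the pooled spread in severity is therefore simply the difference between the groups. A model that recognises the group and outputs one value for each recovers that part, yet says nothing about who is more severely affected within a group.

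MAE and RMSE pooled over both groups do not separate these two sources. Without a reference error, a reader cannot tell how much of the accuracy would be available from the group label alone. Model selection on the same pooled error can also favour the model that best separates the groups.

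At stake is what the severity analysis adds to the classification analysis. Predicting severity among depressed people is a different and harder claim than telling them from controls. This bears on the diagnostic aim, not on the primary efficacy comparison.

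**Working it through.** **The article's own figures.** It gives no figure for the regression, so none can be reproduced. Group sizes follow from Participants: 4 conditions × 32 = 128 per diagnostic group, 256 in total. The test set is 20% of 256 = 51.2, so about 52, of whom about 26 are depressed.

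**Assumed inputs (not in the article).** Gap between group means D = 8, 12 or 16 points; SD pairs (depressed s1, control s2) of (5, 3), (6, 3) or (7, 4). Central case: D = 12, SDs 6 and 3.

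**Formulas.** For two equal groups, let B = D²/4 and W = (s1² + s2²)/2.

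- Predicting the grand mean: RMSE = √(B + W).
- Predicting only the mean of the assigned group, with sensitivity = specificity = a: RMSE = √(B + W − (2a − 1)²B).
- At a = 0.8, (2a − 1)² = 0.36. With a perfect label it is 1.

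**Central case.** B = 144/4 = 36 and W = (36 + 9)/2 = 22.5.

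- Grand mean: √58.5 = 7.6.
- Group-only at 80%: √(58.5 − 12.96) = √45.54 = 6.7, about 12% lower.
- Group-only, perfect label: √22.5 = 4.7, about 38% lower.

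**Ends of the assumed range.**

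| D; SDs | Grand mean | Group-only at 80% | Reduction | Perfect label | Reduction |
|---|---|---|---|---|---|
| 8; 7, 4 | √48.5 = 6.96 | √42.74 = 6.54 | 6% | √32.5 = 5.70 | 18% |
| 16; 5, 3 | √81 = 9.00 | √57.96 = 7.61 | 15% | √17 = 4.12 | 54% |

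**MAE.** Simulating normal scores with D equal to twice the depressed SD and the control SD half as large (the central case in units of 6 points) gives 1.088 for the grand mean, 0.877 at 80% and 0.598 with a perfect label. Multiplied by 6, these are 6.5, 5.3 and 3.6 points, reductions of 19% and 45%.

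**Error within the depressed group, central case.**

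- Perfect label: every depressed participant receives the group mean, so RMSE is the full SD, 6.0.
- At 80%: the prediction lies 0.2 × 12 = 2.4 points from the group mean with probability 0.8, and 0.8 × 12 = 9.6 points with probability 0.2. RMSE = √(36 + 0.8 × 5.76 + 0.2 × 92.16) = √59.04 = 7.7.
- Check: controls give 9 + 23.04 = 32.04, and (59.04 + 32.04)/2 = 45.54, the pooled value above.

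So pooled RMSE improves by 12% while error among depressed participants is 7.7, against 6.0 for simply predicting their group mean. Only the within-group comparison reveals this.

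**Precision.** With 26 normal errors and an RMSE of 6.0, the 95% interval is 6 × √(26/41.92) to 6 × √(26/13.84), or 4.7 to 8.2.

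**The case against.** The strongest reply is that nothing here is false. MAE and RMSE are standard metrics, severity over the full range including healthy people is a legitimate target, and a condensed article may leave baselines and subgroup breakdowns to a fuller plan. The article does not say that these are the only figures to be reported, nor that any particular error would count as success. The analysis is also an additional one.

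Much of this stands, and it sets the tone: the point is about interpretation, not an error of method. It does not dispose of the point. The article itself fixes the metrics and the basis for model selection, and the same section supplies a benchmark and a null for classification but neither for regression. The Efficacy section's plan to add diagnostic group as a between-subject factor concerns the efficacy models and yields no within-group prediction error.

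A reader might infer more than the article supports:

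- **That a group-only model will show a low error, explaining 33% to 79% of the variance.** Those shares are R², which the plan does not use, and they require a perfect group label. At 80% sensitivity and specificity they become 0.36 times as large, 12% to 28%. "Low" also has no meaning here until a comparator is named.
- **That severity must be strongly two-peaked.** The depression group enters by diagnosis with no severity floor, dysthymia and adjustment disorder are included, and controls may score up to 9 on the PHQ-8. Under normal distributions, four of the nine assumed combinations have a single peak (all three at D = 8, and D = 12 with SDs 7 and 4).
- **That the authors already claim to monitor severity on the strength of this regression.** The Discussion speaks of monitoring as a prospect of automated detection and does not tie it to these error metrics.

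**Conclusion.** The concern holds in a limited form. As written, pooled MAE and RMSE without a comparator cannot distinguish a model that measures severity from one that only recognises the group. The direction holds for any gap in mean severity and any group recognition better than chance.

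The size is moderate at the article's own classification benchmark, an RMSE about 6% to 15% below the grand-mean predictor, and grows with classification accuracy to 18% to 54% with a perfect label. These figures rest on assumed gaps and SDs on an unnamed scale, and on reading the regression as using both diagnostic groups, which the article implies but does not state outright. The remedy is worth adopting because it changes what may be concluded and costs almost nothing.

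**What to change.** 1. Keep the pooled MAE and RMSE, and report beside them the same metrics for a grand-mean predictor and a two-group-mean predictor, with means taken from the training set.
2. Report MAE and RMSE within each diagnostic group against the error of predicting that group's training-set mean, with confidence intervals.
3. Describe the result as predicting severity among depressed people only if the within-depression error is below its reference by more than its uncertainty. Otherwise describe it as group discrimination.
4. State that the regression uses both groups, if that is the intention, and name the severity instrument.

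The cost is a few extra lines of analysis on predictions that will exist anyway; no new data are needed. The drawback is precision: the within-depression figure rests on about 26 test participants (half of 20% of 256), and the interval of 4.7 to 8.2 around an RMSE of 6.0 shows how wide it would be. For that reason it should stand beside the pooled error and not replace it as the sole endpoint, and a merely lower value should not be enough for a claim.

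### The best of at least five algorithms is selected, but the only evaluation data described are one 20% test set, so on the plain reading the winner's reported performance is optimistic

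*Protocol article*

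**What the plan says.** All of this is in the protocol article, Statistical analysis plan, under Automated detection of depression, unless noted.

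- **Candidates.** For classification, "different machine learning pipelines will be trained". The models to be evaluated, for classification and regression alike, are given as examples: "k-Nearest Neighbour, Support Vector Machines, Decision Trees, Random Forests, and Artificial Neural Networks". Five is therefore the minimum.
- **Data.** The split uses the "train_test_split function with a fixed random seed", "allocating 80% of the dataset for model training and reserving 20% for evaluation". Only a training set and a test set are named. The article adds that this approach makes performance estimates reliable and protects against overfitting.
- **Selection.** The models are evaluated "to select the best-performing model based on predefined error metrics".
- **Success criteria.** Sensitivity and specificity carry a benchmark of 80%. Separately, "we will test whether the balanced accuracy" exceeds a null distribution, whose construction is not given. For regression, the metrics are MAE and RMSE, with no test against chance.
- **Size.** Under Participants: "we will include *N* = 256 participants in total".

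**The concern.** A test set gives an unbiased estimate only for a model that was fixed before the test set was used. If several models are scored on it and the best is kept, the winner's score is a maximum. It contains the model's true performance plus whatever chance favoured that model in those particular people. With a test set this small the chance part is large.

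The article uses one word for both activities: 20% is reserved for evaluation, and models are evaluated in order to pick one. No third set, inner cross-validation or nesting is mentioned, although the split is specified down to library function, seed and ratio. The weakness remains even if the split is made perfectly at participant level.

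At stake is the detection result. Both success criteria, the 80% benchmark and the comparison with chance, would be easier to meet than they appear. For regression, the winner's MAE and RMSE would look too small. No untouched data would remain to reveal any of this.

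**Working it through.** The article gives no sample size or error rate for the machine-learning part, so there is no stated figure to reproduce beyond N.

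**Inputs from the article.** N = 256; 20% test fraction; at least 5 algorithms; 80% benchmark on sensitivity and on specificity; alpha 0.05, one-tailed where the direction is specified (Efficacy subsection).

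**Assumptions.** Split by participant; test set balanced between diagnostic groups; five equally accurate models; latent correlation of errors between models 0.3 to 0.7.

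**1. Test set size.** 0.20 × 256 = 51.2, rounded up to 52, so 26 per diagnostic group.

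**2. One prespecified model, exact.**
- Chance test: P(X ≥ 33 | n = 52, p = 0.5) = 0.035, and P(X ≥ 32) = 0.063. The one-sided 5% test therefore needs 33 of 52 correct (balanced accuracy 0.635) and has attained size 3.5%.
- Benchmark: 80% of 26 is 20.8, so 21 correct are needed in each group. With a true rate of 0.70, P(X ≥ 21 | n = 26) = 0.1626. Both groups pass with probability 0.1626² = 0.026.

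**3. Best of five on the same 52 people.** Each model classifies a case correctly when a normal variable, partly shared between models, falls below the threshold for its true accuracy. The winner has the highest balanced accuracy, with ties broken at random (40,000 replicates per setting).

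| Error correlation | True 0.70: winner's mean balanced accuracy | True 0.70: sensitivity and specificity both ≥ 80% | No signal: winner's mean balanced accuracy | No signal: winner reaches 33/52 |
|---|---|---|---|---|
| 0.3 | 0.766 | 11.1% | 0.572 | 15.1% |
| 0.5 | 0.760 | 10.4% | 0.566 | 14.0% |
| 0.7 | 0.753 | 9.5% | 0.557 | 12.4% |
| 0.9 | 0.739 | 7.2% | 0.542 | 9.6% |
| One prespecified model | 0.70 | 2.6% | 0.50 | 3.5% |

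Check on the last column: five independent models would give 1 − (1 − 0.0352)^5 = 0.164, so the simulated values lie below that bound, as they should.

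**4. Check with the named algorithms.** The five algorithms were run on pure noise (256 cases, 30 features, both assumed; stratified 80/20 split; 1,500 runs), with selection on the 20%. The winner's mean balanced accuracy was 0.574 and it reached 33/52 in 15.4% of runs.

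**5. Unequal models.** With true accuracies of 0.60, 0.63, 0.65, 0.67 and 0.72 (assumed) and correlation 0.3 to 0.7, the winner's optimism falls from about 5 to 6.5 points to about 3 to 5 points.

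**The case against.** The strongest reply is that the article names the selection criterion but not the data to which it is applied. Cross-validation inside the 80% would be compatible with every sentence, and a condensed article may leave inner resampling to a fuller plan. This stands in part: use of the 20% for selection is the natural reading, but it is not explicit. It does not dispose of the point. The article goes beyond silence: it sets out a procedure in detail and vouches for the reliability of its estimates, and that assurance holds only if selection takes place elsewhere.

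Several stronger readings are tempting, and the document does not support them:

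- **That the chance test is certainly too liberal.** The null distribution is undefined. A permutation null that repeats the whole selection would be valid, although the point estimates would remain optimistic. The 12-15% figure is therefore conditional, and it concerns classification only.
- **That the 80% benchmark can be judged on balanced accuracy.** On that metric the best of five reaches 0.80 in 19-23% of trials, against 5-6% for one model. The article attaches the benchmark to sensitivity and specificity, which gives the lower figures used here. The roughly fourfold ratio is similar.
- **That adding modalities multiplies the candidates to about 15.** The article adds modalities in sequence and calls the full multimodal approach a long-term goal. It says nothing about picking the best modality set.
- **That half of the trial's purpose is at risk.** Detection is introduced as a further aim. The primary outcome is depressed mood, and the sample size was set for comparisons between conditions.

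It is also fair to say that equal true accuracy is the unfavourable case; step 5 of the working shows the reduction.

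**Conclusion.** The point holds in this form: one train-test split combined with a pick-the-best rule and no described validation layer gives optimistic performance for the selected model, contrary to the article's own assurance. For five equally accurate models at 0.70, the optimism is about 5 to 7 points of balanced accuracy, and meeting the benchmark on both sensitivity and specificity becomes about four times as likely (about 10-11% against 2.6%). If a single-model null is used, the false-positive rate of the chance test rises from 3.5% to about 12-15%. MAE and RMSE are biased downwards by the same mechanism; their bias was not quantified.

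These sizes rest on a balanced participant-level test set of 52 and error correlation of 0.3 to 0.7. They shrink with higher correlation or unequal models. They vanish if selection is in fact confined to the training data, which the article should then say. The comparisons of the four study conditions are untouched.

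**What to change.** Amend the Automated detection of depression subsection before the held-out data are used:

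1. Choose the algorithm, hyperparameters and features only within the training 80%, by cross-validation that keeps each participant in one fold.
2. Apply the single selected pipeline once to the held-out 20%, and report sensitivity, specificity, balanced accuracy, MAE and RMSE from that one application. Nested cross-validation over all participants is the alternative.
3. State how the null distribution is built. With one locked pipeline and an untouched test set, a single-model null is valid. If nested cross-validation is used with a permutation null, repeat the whole selection in every permutation.
4. Tabulate the non-selected algorithms, if wanted, as descriptive results only.

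If selection inside the training data was always intended, one sentence saying so resolves the main point. The cost is some extra text, more computing time and a somewhat less favourable reported accuracy. No new data or design change is needed.
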